### Participant timeline {13}

The participant timeline is shown in Fig. 2. An alternative depiction following the SPIRIT schedule recommendation is shown in Fig. 3.

**Fig. 2 Fig2:**
[figure not shown]
Patient journey and intervention assessment timeline; LMS, learning management system; GP, general practitioner

**Fig. 3 Fig3:**
[figure not shown]
Schedule of enrolment, interventions, and assessments following the SPIRIT guidelines

### Sample size {14}

The sample size was calculated for a randomized single-factor ANOVA design with 3 groups without clustering, assuming 30 days of illness (standard deviation of 10 days) during 180 days of follow-up in the control group and a reduction by 4 days for the high-intensity intervention (effect size of Cohen’s *d* = 0.4) and a reduction by 1 day in the medium intensity group. Such reduction was deemed by occupational health physicians as well as general practitioners as clinically highly relevant. Compared to the control group, a power of 80%, a type 1 error probability of less than 5%, and a dropout rate of 25% result in a required sample size or *N* = 151 per group. Thus, we aim to include at least *N* = 453 patients. In order to be able to exclude possible correlations due to socio-demographic variables corresponding to the location of participating practices (in particular rural doctors versus urban infrastructure), the target size is an increased sample size of 600 patients in total (*N* = 200 patients per study arm).

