##### High-intensity intervention

Participants are provided a 12-week closed-group online workshop (webinar) combined with a 12-week interactive digital self-study course that delivers similar and complementary content. The webinar consists of 12 sessions, each approximately 45–90 min, once a week on fixed dates, with 15–25 people per group. The groups, webinar coaches, and dates are constant. Static information materials are additionally provided. This static information material is defined as having not been didactically optimized and laypersons could find the information themselves with intensive literature or Internet search.

The webinars and the self-study course are structured into 12 modules, which build upon each other in terms of content and are completed in chronological order. Each module addresses a specific topic based on typical complaints of patients with post-COVID-19 disease. Central topics among others include coping with everyday life, structuring the day, increasing or pacing physical activity and the ability to relax, coping with pain, promoting acceptance and a positive basic attitude, improving cognitive performance, and the ability to regulate emotions.

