### Statistical methods

#### Statistical methods for primary and secondary outcomes {20a}

Generalized linear models will be used to compare the distribution of primary outcomes (sick leave days) in the randomization groups. Link function will be determined based on the observed sample distribution (we expect Poisson or Negative Binomial distribution). Secondary outcomes will be analyzed by Repeated Measurements Analysis of Variance and Mixed Models for Change analysis. Longitudinal response curves will be visualized by graphs showing the marginal estimates in the randomization groups. All statistical analysis will be conducted using the software package STATA (StataCorp. 2019. Stata Statistical Software: Release 16. College Station, TX: StataCorp LLC).

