One core question is to what extent can psychological online intervention influence the post-viral manifestation of symptoms and help patients regain their ability to work? Considering the WHO’s definition of health as not only the absence of disease or infirmity, but also as a state of complete physical, mental, and social well-being, the biopsychosocial model on which the definition is based is an obvious choice for understanding post-COVID-19 condition as a disorder model. The clinical picture of Long COVID includes a wide range of physical, psychological, and social symptoms and is accompanied by a significant decrease in well-being. In this respect, it can be assumed that the Long COVID symptom bundle undergoes a significant overall improvement of the general state of health through systematic treatment of the main areas of the disorder. Which of the 12 thematically different modules, or which combination of them, can most accurately map a specific mechanism of action is therefore of major interest. On the other hand, it is known from many studies on the treatment of chronic physical illnesses that adjuvant psychological therapy and social support can be highly effective in alleviating somatic complaints. It will be interesting to investigate the effect of the social support provided by the psychological coach and the webinar group in the high-intensity intervention arm compared to the simple availability of the learning content through the LMS.

Of course, it is nevertheless possible that the program is not perceived as individualized or broad enough, despite the wide range of content. This could lead to disappointment, excessive demands, and dropout and negatively impact potential effects.

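### The high-intensity arm is delivered in fixed webinar groups, but the sample size excludes clustering and the named primary model has no group term; if outcomes correlate within groups, that arm's standard errors are too small

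*Protocol article*

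**What the plan says.** Under High-intensity intervention, the protocol article describes a closed-group online workshop of 12 weekly sessions with 15–25 people per group, and adds: "The groups, webinar coaches, and dates are constant". The Moderate intensity intervention and Control sections describe self-paced access without webinars, so participants in those arms belong to no group.

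Under Sample size {14}: "The sample size was calculated for a randomized single-factor ANOVA design with 3 groups without clustering". The inputs are "assuming 30 days of illness (standard deviation of 10 days) during 180 days of follow-up in the control group", "a reduction by 4 days for the high-intensity intervention" and "a reduction by 1 day in the medium intensity group", with 80% power, 5% type I error and 25% dropout. This gives 151 per group (453 in total). The target is then raised to 600 (200 per arm), for a reason tied to the location of the practices and not to the webinar groups.

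Under Statistical methods {20a}: "Generalized linear models will be used to compare the distribution of primary outcomes (sick leave days) in the randomization groups". Mixed models are mentioned for the secondary outcomes only, and no webinar-group level is named there either.

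Two further sections bear on whether groups will differ. Possible conceptual risks says that high-intensity participants choose their webinar group after randomization, and that content opens only once the group has filled, which may take long. Plans for assessment {18a} counts the six months of sick leave from registration in the platform.

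**The concern.** This is a partially nested design: one arm is clustered by treatment delivery and two are not. People in one webinar group share a coach, peers, a calendar period and a waiting time. They also chose the group themselves, so people with similar working hours or circumstances may end up together. The waiting time matters most for the primary endpoint, because the outcome clock starts at registration. A group that fills slowly has less treated time inside the six-month window than one that fills quickly, and every member shares that loss.

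If any of this makes outcomes more alike within a group than between groups, the mean of the high-intensity arm is less precise than its head count suggests. A model without a group term then gives too small a standard error for high intensity versus control and for high versus moderate intensity. The abstract presents the first of these as the comparison the trial is powered for, and the introduction wants the result to help justify the costlier intervention. An error that favours false positives in that arm is therefore badly placed. A negative binomial dispersion parameter does not help, because it describes extra variation between individuals and not correlation among members of a group.

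**Working it through.** **Inputs.** From Sample size {14}: means of 30, 29 and 26 days, SD 10, alpha 0.05, power 80%, dropout 25%, 151 per arm as minimum and 200 per arm as target. (The abstract gives an effect size of 0.3 and 152 per arm; the Sample size section is used here.) From High-intensity intervention: 15–25 per group. The ICC is not in the document, so 0.01, 0.02, 0.05 and 0.10 are assumptions.

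**Step 1: reproduce the plan's figure.** Unclustered one-way F test with three groups. The grand mean is 28.33 and the squared deviations sum to 8.667. The noncentrality is n × 8.667 / 100. At n = 113 it is 9.79 and power is 80.3%; at n = 112 power is 79.9%. So 113 evaluable per arm are needed, and 113 / 0.75 = 150.7, rounded up to 151. The stated figure reproduces exactly and contains no allowance for webinar groups.

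**Step 2: variance under partial nesting.** With m analysed per webinar group, the design effect in the high-intensity arm is DE = 1 + (m − 1) × ICC; in the control arm it is 1. Hence

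- Var(difference) = (SD² / n) × (1 + DE)
- true SE / naive SE = √[(1 + DE) / 2]
- real two-sided error = 2 × Φ(−1.96 / that ratio)
- power for 4 days = Φ(4 / SE − 1.96)

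Example, m = 15, ICC 0.05: DE = 1 + 14 × 0.05 = 1.70; ratio = √(2.70 / 2) = 1.162; error = 2 × Φ(−1.687) = 9.2%.

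**Step 3: real type I error of a nominal 5% test that ignores groups, high intensity versus control.**

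| ICC (assumed) | 15 per group | 20 per group | 25 per group |
|---|---|---|---|
| 0.01 | 5.8% | 6.1% | 6.4% |
| 0.02 | 6.6% | 7.2% | 7.8% |
| 0.05 | 9.2% | 10.7% | 12.1% |
| 0.10 | 13.3% | 16.0% | 18.6% |

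The number enrolled does not enter this ratio, so moving from 453 to 600 leaves the table unchanged. A simulated three-group F test that ignores groups (150 per arm, 15 per group) agrees: 6.2%, 9.3% and 12.9% at ICC 0.02, 0.05 and 0.10.

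If 25% of each group drops out, groups of 15–25 leave about 11–19 analysed. The lower end is then milder (m = 11.25, ICC 0.05: DE = 1.51, error 8.0%). A group of 20 with 25% loss gives the 15-per-group column.

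**Step 4: power for high intensity versus control with the correct SE.**

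| ICC | 113 evaluable, m = 15 | 150 evaluable, m = 15 | 150 evaluable, m = 20 | 150 evaluable, m = 25 |
|---|---|---|---|---|
| 0.02 | 80.4% | 90.0% | 88.8% | 87.5% |
| 0.05 | 73.5% | 84.6% | 81.4% | 78.2% |
| 0.10 | 63.5% | 75.7% | 69.9% | 64.6% |

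Here 150 is 200 × 0.75. Setting power to 80% requires 1 + DE = n × 0.16 / (1.96 + 0.84)², which is 3.06 at n = 150. The break-even ICC is therefore about 1.06 / (m − 1): 0.076, 0.056 and 0.044 for 15, 20 and 25 per group. At n = 113 it is 0.022, 0.016 and 0.013.

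**Step 5: number of groups.** 200 / 25 = 8 and 200 / 15 = 13.3, so about 8–13 groups. The normal approximation above is optimistic with so few, and a proper small-sample test would lose somewhat more power than Step 4 shows.

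**The case against.** Four points on the other side deserve weight.

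**Power at the target.** A reader might infer that the trial's stated power is simply too high. The document does not support that as a general statement. The target is 600, and at 150 evaluable per arm the stated 80% holds up to an ICC of about 0.05 for groups of 15–20. The shortfall belongs to the 453 minimum, to groups of 25 at an ICC of 0.05, or to larger ICCs. The objection stands for power. It does not reach type I error, which the larger enrolment leaves untouched.

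**Group effect versus group variation.** The Discussion wants to study "the effect of the social support provided by the psychological coach and the webinar group in the high-intensity intervention arm", which might be read as proof that outcomes are correlated within groups. It is not: it describes an average benefit of having a coach and peers, compared with content alone. Correlation needs groups to differ from one another. The article also describes standardized coach training, a detailed manual and supervision, all of which would reduce such differences. The case for correlation rests instead on self-chosen groups and unequal waits inside the outcome window, which coach training cannot remove.

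**Unknown ICC, distant endpoint.** Sick leave certified by each patient's own physician over six months lies further from the webinar than a symptom score, so the ICC may be low. At 0.01 the real error is only about 6%. This is a fair limit on the size of the problem, but the article offers no ground for assuming a value that low.

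**The analysis plan may deal with it.** Only the sample-size sentence excludes clustering outright. The analysis section names a model without a group term but does not say that participants are treated as independent, and an analysis plan that is not shown could add one. What stands is that the plan as written, if followed, ignores the groups.

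**Conclusion.** The concern holds in conditional form. One arm is clustered by delivery, the sample size explicitly leaves this out, and the named primary model does not include it. Whenever the within-group ICC exceeds zero, the standard errors for comparisons with the high-intensity arm are too small.

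The size depends on an ICC that the document does not give: close to negligible at 0.01, and roughly a doubling of the nominal 5% error at 0.05. The figures use the protocol's own mean and SD on the normal scale; a count model would change their size but not their direction. The 600 target protects power reasonably well up to an ICC of about 0.05 for groups of 15–20, before any loss from having few groups. The 453 minimum does so only up to about 0.02. It would go too far to say that the trial will report false significance or is underpowered as planned.

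**What to change.** Analyse primary and secondary outcomes with a partially nested model: a random effect for webinar group in the high-intensity arm only, each participant in the other two arms treated as a singleton, and a small-sample correction suited to roughly 8–13 groups. Keep the webinar-group identifier in the end-of-trial export from the learning platform; since participants choose their group there after registration, it is probably already recorded. Restate power for both the 453 minimum and the 600 target over a stated ICC range and group size. Settle the model before outcome data are analysed.

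The cost is some wording in the analysis plan, one variable in the export, and somewhat wider intervals for the high-intensity arm. Enrolment and the interventions stay as they are.

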## Introduction

### Background and rationale {6a}

Following initial infection with SARS-CoV-2, a considerable proportion of patients suffer from a variety of persisting or de novo occurring symptoms, known as post-COVID-19 condition or Long COVID. Depending on the definition used, the unadjusted prevalence reported in the literature varies substantially [1–5]. The persistence of at least some COVID-19-associated symptoms is described for up to 60% of non-hospitalized patients or those with mild initial clinical course [6, 7]. While these early figures derived from infections with pre-Omicron variants may not reflect current prevalence, even under conservative assumptions, an adjusted prevalence of 12.7% among previous COVID-19 patients must be expected in the community setting [8].

The severity distribution appears to be skewed with a larger proportion of affected patients experiencing mild to moderate symptoms that impair work ability and quality of life, but do not render these patients fully incapable of daily life activities. However, the impact on work ability implies a substantial public health and economic burden for society, given the millions of people affected across Europe.

Long COVID comprises a staggering multitude of symptoms, e.g., fatigue, brain fog, anxiety, depression, shortness of breath, headache, cough, impaired sleep, dizziness, neck, joint, chest and general muscle pain, hair loss, and very often impaired daily activity [1, 4, 6–10]. Hence, Long COVID impairs cognitive and physical performance as well as quality of life. Particularly those with prolonged and severe fatigue, neurocognitive impairment, depression, or pain experience substantially impaired work ability [11]. An international study from 56 countries reported that about one in five individuals suffering from Long COVID symptoms were unable to work due to the illness, while almost half had to reduce their working hours [12]. The largest German statutory health insurance reported an average of 105 sick leave days per year (p.a.) for severe Long COVID patients compared to the population average of 14.6 sick leave days [13]. For Germany, the economic burden of lost production and the lost gross value added arising from incapacity to work is estimated as a combined national economic loss of approx. 350 € per day of sick leave [14]. Similar calculations for the entire US estimate the total economic burden of lost work due to Long COVID to 175 billion US$ annually [15].

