### Outcomes {12}

#### Primary outcome

Primary outcome is the cumulative sum of sick leave days in patients during the period from enrollment to 6-month follow-up. We compare the high-intensity intervention versus moderate-intensity intervention versus control group. In Germany, every employee requires a medical sick leave certificate. The medical sick leave certificate entitles to 6 weeks of continuous payment of the salary by the employer. Thereafter, for additional 180 days, the statutory health insurance provides 80% of the net salary. Law mandates that employers offer employees with sick leave of longer than 6-week duration the opportunity to participate in a structured employment reintegration program (BEM). In such programs, patients are attempted to be reintegrated into their former jobs in agreement with the occupational health physician, the employer, and the employees’ representative board. The usual process is to gradually increase the weekly job hours and job requirements expressed as a percentage of full employment. Therefore, if a patient takes part in such a program, the sum of days that the participant has spent within an integration percentage stage is used as the primary outcome instead (e.g., 10 working days at 50% equals 5 days on full sick leave). In both cases—sick leave days and reintegration days—the data is reported directly to the study management by treating GPs via their health care networks at once at the end of the trial.

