The integration of a therapeutic and a preventive approach in the inclusion criteria also involves the risk of varying adherence and dropout. The motivation of already chronically ill patients to make every effort to get well is expected to be much higher than the efforts of acutely ill patients to not necessarily develop Long COVID. Yet, in general, most illnesses such as back pain or depression benefit from early intervention. Moreover, the public perception and also the diagnostic handling of COVID-19 in the healthcare system are currently changing in the expiring pandemic situation. Many cases remain undiagnosed due to the changed guidelines and therefore evade the inclusion criteria in the prevention criterion. In our experience, the overall awareness of the problem is decreasing and similarly the motivation to take preventive measures. The perception of Long COVID as a serious disease varies widely among the population and it is known that only a subset of those infected with SARS-CoV-2 develop a post-COVID-19 condition. Finally, it is generally difficult to show the effectiveness of preventive measures. All this could lead to an underrepresentation of the preventive approach.

A fundamental challenge lies in the expected heterogeneity of the patient sample. Health programs typically benefit from a target group-specific approach. Different levels of education, different experiences with the use of digital media, and their acceptance can influence the effects. Since MiLoCoDaS specifically addresses a cross-section of the population, this perspective could not be taken into account. The intention is to represent conditions as they are found in routine patient care, to lead to the development of a realistic therapy scheme. Therefore, exploratory secondary analyses have been formulated. The bottom line for society is whether such digital intervention and the efforts related to this are cost-effective. Experts in occupational medicine rendered a reduction in sick leave by more than half a week on average as a relevant improvement warranting to include the intervention into the therapeutic armature [46]. We approximated this from the available data as a 4-day reduction at an average duration of 30 days with a standard deviation of 10 days.

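### The 80% power rests on a control SD of 10 sick-leave days that the protocol does not support and that is very probably too small for the mixed population admitted

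*Protocol article*

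**What the plan says.** Sample size {14} bases the calculation on a "randomized single-factor ANOVA design with 3 groups without clustering". For the comparator it works from this premise: "assuming 30 days of illness (standard deviation of 10 days) during 180 days of follow-up in the control group". The most intensive arm is given "a reduction by 4 days for the high-intensity intervention", which the section equates to d = 0.4; for the middle arm the figure is "a reduction by 1 day in the medium intensity group". With 80% power, a type 1 error below 5% and 25% dropout it arrives at 151 per group, 453 in total. The target is then raised to 600 (200 per arm). The reason given is socio-demographic differences between practice locations, not doubt about the SD.

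The Limitations section gives the origin of the figures: "We approximated this from the available data as a 4-day reduction at an average duration of 30 days", with the same SD of 10. It also calls the expected heterogeneity of the sample a fundamental challenge.

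The Methods part of the Abstract gives a different basis for the same 80%: Cohen 0.3 between the augmented and the sham arm, with 152 per arm and 600 in total after allowing for attrition.

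**The concern.** A mean of 30 with SD 10 puts about 95% of control patients between 10 and 50 days (30 ± 1.96 × 10) on a scale from 0 to 180. The rest of the protocol describes a wider spread.

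- **Eligibility criteria {10}:** the treatment path asks for an infection at least 3 months ago plus a diagnosis or symptoms, and no sick leave. The prevention path asks for persisting incapacity for work. Two different sick-leave populations share one mean.
- **Outcomes {12}, Primary outcome:** there is a special counting rule for reintegration programmes. Employers must offer "employees with sick leave of longer than 6-week duration the opportunity to participate in a structured employment reintegration program", so some long absences are expected.
- **Background {6a}:** in an international study "about one in five individuals suffering from Long COVID symptoms were unable to work due to the illness". A German insurer reports "an average of 105 sick leave days per year (p.a.) for severe Long COVID patients compared to the population average of 14.6".

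The SD is the input to which the sample size is most sensitive. If it is too low, the trial has a poor chance of detecting the 4-day reduction that the protocol calls clinically highly relevant, and a non-significant result could be mistaken for evidence that no such benefit exists.

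**Working it through.** **1. Reproducing the plan's figure.** Inputs from Sample size {14}: means 30, 29, 26; SD 10; alpha 0.05; 25% dropout.

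Grand mean = 85/3 = 28.33. Sum of squared deviations = 1.667² + 0.667² + 2.333² = 8.667.
Noncentrality λ = n × 8.667 / SD². For n = 113 and SD 10, λ = 9.79 with 2 and 336 degrees of freedom, critical F 3.02, power 80.3%. Then 113 / 0.75 = 150.7, so 151. The stated number is correct on its own inputs.

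**2. What SD 10 implies.** Statistical methods {20a} expects a Poisson or negative binomial outcome. For a negative binomial, variance = mean + k × mean², so 100 = 30 + 900k and k = 0.078. That distribution puts about 2 in 10 million patients at zero days, about 11% above 42 days and about 0.6% above 60.

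**3. Smallest possible SD at mean 30.** Put a share q at one extreme and let everyone else have the same number of days. This is the case most favourable to the plan.

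- Share q at zero: SD ≥ 30 × √(q/(1−q)). q = 10% gives 10.0, 20% gives 15.0, 30% gives 19.6.
- Share q at 180: SD ≥ (180 − 30) × √(q/(1−q)). q = 0.5% gives 10.6, 1% gives 15.1.
- Share q at 129, if only working days count (assumed 5 per week, 180 × 5/7 ≈ 129): q = 1% gives 99 × 0.1005 ≈ 9.9.

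SD 10 therefore needs at most 10% of patients with no sick leave and, on a 180-day count, fewer than about 0.5% absent throughout. Any variation among the remaining patients raises the SD further.

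**4. Power and detectable difference over an assumed range.** Analysable per arm: 113 (151 enrolled) and 150 (200 × 0.75). Detectable difference for one pair at 80% power = (1.960 + 0.842) × SD × √(2/n).

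| SD | F-test power, 113 / 150 | High vs control power, 113 / 150 | Detectable difference in days, 113 / 150 |
|---|---|---|---|
| 10 | 80% / 91% | 85% / 93% | 3.7 / 3.2 |
| 13.3 | 54% / 67% | 62% / 74% | 5.0 / 4.3 |
| 15 | 44% / 56% | 52% / 64% | 5.6 / 4.9 |
| 20 | 27% / 34% | 32% / 41% | 7.5 / 6.5 |
| 30 | 14% / 17% | 17% / 21% | 11.2 / 9.7 |

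The largest SD that still gives 80% is 10.0 (F test) or 10.7 (pairwise) at 113, and 11.6 or 12.4 at 150.

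**5. The Abstract.** If the effect is still 4 days, Cohen 0.3 means SD = 4/0.3 = 13.3. Pairwise power at d = 0.3 is Φ(0.3 × √(n/2) − 1.96). This gives 74% at 150 to 152 per arm, and 62% at 114 (152 less 25%, if 152 is an enrolled number). Neither reaches 80%.

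**The case against.** A reader might infer that the enrolled population cannot have an SD as small as 10, and that the trial will fail to deliver 80% power. The documents do not support either statement.

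- No SD, zero share or long-absence share is given for the patients enrolled. The shares used above are assumptions.
- The 105 and 14.6 days a year are means for severe cases and the general population. The one-in-five figure is not limited to mild or moderate cases. This trial excludes patients hospitalised for COVID-19 or repeatedly treated by specialists for it, and the Discussion describes its patients as not fully incapacitated. Mixing the half-year values 7.3 and 52.5 to a mean of 30 (weight 0.50) gives SD 22.6, but that only illustrates two groups who are not the trial population.
- The worked example in the primary outcome counts working days. On such a count the 1% floor falls just below 10, and weighting reintegration days by percentage shortens long absences further.
- The reintegration rule applies only to those who join a programme. A provision for absences over 42 days is compatible with SD 10, which already puts about 11% there.
- At the 600 target, power is 91% at SD 10, so there is some slack.
- Poisson, one of the two distributions the plan expects, would mean an SD of only 5.5.
- The article is condensed, and the data behind the SD may be documented elsewhere.

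Most of this stands, and it limits the conclusion to one of plausibility. It does not restore the assumption. Poisson at mean 30 requires every patient to share one rate, which the two entry paths and the acknowledged heterogeneity make unlikely. The slack at 600 ends at SD 11.6. The zero-day floor does not depend on how many days can be counted.

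**Conclusion.** The calculation is right and the input is weak. SD 10 is unsupported in the text and very probably too small for the population admitted, so 80% power is not established. At the 453 minimum there is no margin: any SD above 10.0 takes the F test below 80%. At 600 the margin ends at about SD 11.6 for the F test, or 12.4 for high intensity against control. At SD 15, which 20% of patients at zero days would already force, F-test power is 44% with 113 analysable per arm and 56% with 150.

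The effect size in the Abstract, read with a 4-day effect, itself implies a larger SD (13.3) than Sample size {14} uses, and does not give 80% at the planned size.

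These conclusions rest on a mean of 30, an assumed range of SDs and normal-theory tests. The planned analysis is a generalized linear model, so the percentages only approximate its power. The documents do not say that a non-significant result will be read as no benefit; that is a risk to guard against, not a stated intention.

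**What to change.** 1. In Sample size {14}, state that 80% holds only at SD 10, give the source of that SD, and show power and detectable difference for SD 10 to 30 at 113 and 150 analysable per arm.
2. Reconcile the Abstract (Cohen 0.3, 152 per arm) with Sample size {14} (d = 0.4, 151 per group), and say whether the per-arm numbers are before or after dropout.
3. Compute the pooled SD from the GP totals with arms masked, before allocation codes are merged. Ignoring arms hardly distorts it: under the plan's means and SD 10 the pooled value would be √(100 + 8.667/3) = 10.1. Under {18a} the totals arrive only at the end of the trial, so this documents what the trial could detect and cannot change enrolment.
4. Report the confidence interval for high intensity against control next to the 4-day relevance limit. State in advance that a non-significant result does not exclude a 4-day reduction unless the interval does.

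The cost is wording, one table and one masked calculation. No extra patients are needed. The downside is that the stated power becomes less favourable.
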